## Abstract

**Background:**

The prevalence of chronic disease multimorbidity among Chinese adults is high and presents a serious public health challenge. Personalized and accessible lifestyle interventions are key to improving long-term outcomes. Existing mobile health technologies often deliver generalized content, offering high accessibility but overlooking the potential of individualized interventions informed by Traditional Chinese Medicine (TCM) body constitution. TCM emphasizes identification of constitution types to develop more targeted and comprehensive personalized lifestyle guidance. Therefore, we developed the Artificial Intelligence–Health Education and Lifestyle Support system based on TCM body constitution (AI-HEALS) to explore its feasibility and assess its preliminary efficacy in improving clinical outcomes, enhancing self-management behaviors among patients with chronic disease multimorbidity.

**Methods:**

This study adopts a three-arm parallel randomized controlled trial design. A total of 207 patients with hypertension, type 2 diabetes, and/or hyperlipidemia will be recruited and randomized in a 1:1:1 ratio into a routine chronic disease management group, a generalized AI-HEALS intervention group, or a TCM-based AI-HEALS intervention group. The routine management group will receive standard chronic disease care only. AI-HEALS is deployed via a WeChat Mini Program and features automated health-education content delivery, digital diaries for data logging, and intelligent Q&A functions. The backend houses a knowledge base covering chronic disease multimorbidity and TCM constitution-based wellness. The generalized AI-HEALS group will receive health-education content targeting chronic disease multimorbidity. The TCM-based AI-HEALS group will first complete a constitution assessment through the Mini Program, after which the system will deliver personalized health-management content tailored to their constitution type, drawing from the combined knowledge base of chronic disease multimorbidity and TCM constitution wellness. The intervention will last 3 months with follow-ups to month 6. The primary outcome is the change in systolic blood pressure from baseline to the end of intervention. Secondary outcomes include blood glucose and lipid levels, chronic-disease self-management behaviors, among others. Changes in TCM constitution classification will be treated as an exploratory outcome.

**Discussion:**

This study integrates TCM constitution theory with the AI-HEALS system to provide an innovative, personalized, and accessible management strategy for chronic disease multimorbidity, and seeks to explore the value of combining traditional medical theory with modern information technology. This protocol describes a randomized controlled trial designed to generate preliminary evidence on effectiveness.

**Clinical trial registration:**

https://www.chictr.org.cn/index.html, identifier ChiCTR2600118267

## Background

1

Approximately one quarter of Chinese adults are affected by chronic disease multimorbidity, with hypertension combined with dyslipidemia or diabetes representing the most common patterns of coexistence (1). Hypertension, diabetes, and dyslipidemia are independent major risk factors for cardiovascular disease (2), and when they occur together, the risk of cardiovascular events increases multiplicatively (3). The resulting cardiovascular and cerebrovascular diseases not only severely threaten patients’ quality of life but also impose a substantial economic burden (4, 5). In 2020, total hospitalization costs for cardiovascular and cerebrovascular diseases in China reached 270.901 billion yuan, of which hypertension and diabetes accounted for 13.260 billion yuan and 31.641 billion yuan, respectively. Such multimorbidity has become a serious challenge to public health and socioeconomic development (6).

Individuals’ lifestyle choices and behaviors are deeply rooted in their surrounding sociocultural environment (7). In this context, Traditional Chinese Medicine (TCM) constitution theory provides a time-tested framework for understanding individual differences. It aims to reveal the unique body constitution formed through interactions between innate endowment and acquired environmental influences, and to elucidate its intrinsic relationship with health and disease (8, 9). More targeted and personalized intervention strategies can be developed by accurately identifying one’s constitution type (10, 11). Individuals with phlegm-dampness, blood stasis, or Yin-deficiency constitutions have significantly higher risks of metabolic syndrome compared with those of a more balanced constitution, and these constitution types are positively correlated with key metabolic indicators (12). Interventions such as “strengthening the spleen and resolving dampness” for phlegm-dampness constitution can improve body weight and glycemic control (13), while “nourishing Yin and moistening dryness” for Yin-deficiency constitution may help regulate lipid metabolism (14). Despite differences in specific treatment methods, these approaches commonly involve TCM constitution–based lifestyle-modification guidance—including diet, exercise, daily routine, emotional regulation, and supportive use of Chinese herbal medicine (14). Such interventions have been shown to enhance chronic-disease self-management (15), reduce pharmaceutical medication dependence (16), lower chronic-disease susceptibility (17), and improve quality of life (15). However, traditional healthcare models rely on infrequent, episodic consultations that are costly and limited in continuity and accessibility (18), greatly restricting their scalability. Providing continuous, comprehensive, accessible, and personalized lifestyle interventions for patients with chronic multimorbidity (19) can effectively enhance their self-management capabilities (20) and subsequently improve clinical outcomes in diabetes, hypertension, and dyslipidemia (21). The Constitution in Chinese Medicine Questionnaire (CCMQ), issued by the China Assocition of Chinese Medicine, has demonstared good reliability and validity and is a commonly used of Chinese Medicine, has demonstrated good reliability and validity and is a commonly used instrument for constitution identification (22). While an individual’s constitution exhibits a degree of stability, it can evolve over the life course due to influences from lifestyle and internal or external environments (23). However, most existing studies on constitution are cross-sectional or case–control investigations with small sample sizes, which can suggest but cannot substantiate causal relationships between constitution-based interventions and health outcomes (24). This study is designed as an evidence-building effort to contribute more robust empirical evidence in this area.

The widespread adoption of mobile health technologies has improved the accessibility of healthcare services (25), and numerous studies have demonstrated their positive effects on managing chronic disease indicators such as blood pressure and blood glucose (26–29). However, a detailed examination of these studies (30, 31) reveals that mobile health interventions for chronic diseases typically rely on standard management supplemented with app-based health-education messages. Such approaches overlook the substantial individual differences among patients with chronic multimorbidity, making it difficult to achieve precise, root-cause-oriented regulation tailored to each person (32, 33). Integrating the *individualization* principles of TCM body constitution with the *scalability* and *empowerment* of mobile health technologies may offer a new model of personalized, patient-centered health management.

In response, our research team previously developed the Artificial Intelligence–based Health Education Accurately Linking System (AI-HEALS). AI-HEALS is constructed on the Multitheoretical Model (MTM) framework for health behavior change and comprises two modules—AI-Chatbot and HEALS— which are delivered via the WeChat Mini-Program. The AI-Chatbot module is designed to emulate an “integrative Chinese–Western medicine clinical expert.” It utilizes natural language processing (NLP) technology. Having been pre-trained and fine-tuned on authoritative medical literature (including guidelines, textbooks, and research papers), and iteratively refined through multiple rounds of expert feedback. This enables the module to conduct interactive question-answering with context-aware understanding and semantic reasoning. It incorporates data-driven machine-learning components that support continuous learning and performance enhancement. The HEALS module is responsible for pushing personalized health content to users. It does not rely on machine-learning or adaptive algorithms, but instead on a rule-based decision logic combined with user-behavior data analysis for content matching. Specifically, the system builds a basic interest profile by recording user interaction (e.g., sections clicked, reading duration, and time) and selects appropriate content from an expert-curated knowledge base according to predefined rules (e.g., disease type, intervention stage, TCM constitution classification). Therefore, HEALS functions as a structured, rule-driven decision-support component, with personalization derived from its rule engine and layered content design. Collectively, the system features automated delivery of health-education messages, digital diary functions, and intelligent question-and-answer capabilities. Its backend contains a knowledge base—updated every 3 months—covering chronic disease multimorbidity and TCM constitution-based wellness guidance. A core innovation is the embedded TCM body-constitution assessment module: after users complete the constitution evaluation via the WeChat Mini Program, the system dynamically delivers personalized health-management content based on the TCM constitution wellness knowledge base, while the intelligent Q&A module provides real-time responses to patient inquiries. The aims of this study are as follows:

To evaluate the effectiveness of the AI-HEALS system—particularly its TCM-adapted version—compared with routine management and generalized mobile health interventions in improving clinical outcomes among patients with chronic disease multimorbidity.To assess the effectiveness of the system in enhancing chronic-disease self-management behaviors.

## Methods

2

### Study design

2.1

This study will adopt a single-blind, three-arm parallel randomized controlled trial design. Participants will be recruited from a Class A secondary hospital in Zhejiang Province, China. All enrolled patients will receive standard chronic disease management in accordance with *Expert consensus on standardized diagnosis and treatment of coexisting hypertension, hyperglycemia, and hyperlipidemia in China (2023 edition)* (3). The intervention period will last for 3 months, followed by continued observation until month six to assess the sustainability of short-term effects. The three groups differ in the additional interventions provided:

Control Group (CG): Routine chronic disease management only.Universal AI-HEALS Group (UG): Routine management plus access to the AI-HEALS WeChat Mini Program (universal version).TCM-Adapted AI-HEALS Group (TG): Routine management plus access to the AI-HEALS WeChat Mini Program (TCM-adapted version).

The study flow and group allocation are shown in Figure 1.

**Figure 1 fig1:**
[figure not shown]
Flow chart of patient recruitment and study implementation.

### Participants

2.2

#### Recruitment and sample size

2.2.1

This study plans to use a consecutive enrollment strategy between February 2026 and December 2026. Specialized personnel from the hospital Information Department (not involved in this study) will conduct an initial screening of anonymized data from the electronic health record system to identify patients who meet the diagnostic criteria for multimorbidity. Subsequently, research assistants will independently review the data in pairs based on predetermined inclusion and exclusion criteria. Once eligibility is confirmed, independent recruitment staff will contact potential participants using compliant contact information recorded in the hospital system and invite them to join the study after obtaining informed consent.

The sample size calculation is based on the primary outcome (systolic blood pressure). According to previous similar research (34–36), the optimistic but clinically significant effect size hypothesis was adopted. The expected systolic blood pressure after 3 months of intervention is set as follows: 138.2 mmHg for the routine health education group, 132.0 mmHg for the universal AI group, and 127.0 mmHg for the TCM-constitution–based AI group. The common inter-group standard deviation (*σ*) is set at 16.3 mmHg. Using G*Power 3.1 software with one-way ANOVA (F tests), two-sided *α* = 0.05, and power (1 − *β*) = 90%, the required sample size is 55 participants per group, totaling 165 participants. Considering an estimated 20% dropout rate, the final planned recruitment is 207 participants, or 69 per group. If the true intervention effect size is smaller than the assumed, the statistical power of this study will be correspondingly reduced, and the results should be interpreted with caution and regarded as preliminary exploratory evidence.

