### Statistical analysis

2.7

Statistical analyses will be performed using SPSS 26.0 (or R). Continuous variables with normal distribution will be presented as mean ± standard deviation; non-normally distributed variables as median (interquartile range).

All primary and key secondary analyses will adhere to the intention-to-treat principle. To evaluate the effect of the intervention on health outcomes, under the assumption of data missing at random, a linear mixed-effects model will be applied. Time, group, and their interaction will be included as fixed effects, and a random intercept will be added for each participant to control for baseline heterogeneity. Baseline values and age will be included as covariates.

Between-group differences at each time point will be estimated using the EMMEANS package to compute estimated marginal means (EMMs), followed by adjusted pairwise comparisons (e.g., Tukey multiple comparison tests). To assess overall changes from baseline to the end of follow-up, model-estimated baseline-adjusted marginal means at the endpoint will be compared among the three groups. The family-wise error rate for primary and key secondary outcomes will be controlled using the Bonferroni method. A *p*-value < 0.05 will be considered statistically significant.

Sensitivity analyses will be conducted to assess the robustness of the findings:

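### The stated 90% power belongs to the three-arm omnibus test; for the pairwise contrasts that the plan draws on, TCM-adapted versus universal app stays far below 90% on the plan's own assumptions

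*Protocol article*

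**What the plan says.** - **Sizing (section 2.2.1).** The calculation was made "Using G*Power 3.1 software with one-way ANOVA (F tests), two-sided" alpha 0.05. The expected month-3 systolic pressures are "138.2 mmHg for the routine health education group", "132.0 mmHg for the universal AI group" and 127.0 mmHg for the TCM-based group, with a common SD of 16.3 mmHg. For 90% power, the result is stated as "the required sample size is 55 participants per group, totaling 165 participants", raised to 207 (69 per arm) for 20% dropout. A closing caution says that power will be lower if the true effect is smaller than assumed.
- **Aims (end of section 1).** The system, and in particular its TCM version, is to be "compared with routine management and generalized mobile health interventions in improving clinical outcomes". That is a comparison with each of two comparators.
- **Analysis (section 2.7).** A linear mixed model with group, time and their interaction, and with baseline value and age as covariates, yields marginal means, "followed by adjusted pairwise comparisons (e.g., Tukey multiple comparison tests". A further sentence says that "model-estimated baseline-adjusted marginal means at the endpoint will be compared among the three groups". Bonferroni control is then applied over the primary and key secondary outcomes.

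**The concern.** An omnibus F test asks whether the three means are all equal. It can reject because one pair lies far apart, and it carries no assurance about any particular pair. Here the assumed gaps are 11.2 mmHg (TG-CG), 6.2 mmHg (UG-CG) and 5.0 mmHg (TG-UG), so the 90% is carried mainly by the widest gap.

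The universal arm makes it possible to separate the effect of TCM tailoring from the effect of having an app at all. If that contrast has low power even when the assumed effect is true, a non-significant result is a likely outcome. Set beside a stated 90% power, it would invite the conclusion that tailoring adds nothing. The caution in section 2.2.1 does not prevent this, because it speaks only of effects smaller than assumed. The shortfall exists at the assumed effect.

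**Working it through.** **Inputs from section 2.2.1:** means 138.2 (CG), 132.0 (UG) and 127.0 (TG) mmHg; SD 16.3; alpha 0.05; 55 evaluable per arm; 20% dropout.

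**Assumed, because the document gives no figure:** correlation r between baseline and month-3 pressure, 0.3 to 0.7, taking 16.3 as the SD of month-3 pressure.

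**1. Reproduce the stated figure.** The grand mean is 132.4 and the deviations are 5.8, -0.4 and -5.4.
- f = sqrt((33.64 + 0.16 + 29.16)/3)/16.3 = 4.581/16.3 = 0.281.
- Noncentrality = 165 × 0.281² ≈ 13.03, with 2 and 162 degrees of freedom.
- Noncentral F power is 90.3% at 55 per arm and 89.8% at 54. So 55 per arm is right for this test.
- Dropout: 165/0.8 = 206.25, rounded up to 207; 55/0.8 = 68.75, rounded up to 69. Both reproduce.

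**2. See what carries the 90%.** Moving the UG mean to the exact midpoint of the other two (132.6) leaves omnibus power at 90.2%. The result depends on the TG-CG gap and hardly at all on where UG sits near the middle.

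**3. Power per contrast, no gain from baseline.** The standard error of a difference is 16.3 × sqrt(2/55) = 3.108. Noncentrality is the difference divided by 3.108, with 162 degrees of freedom. The critical value is 1.975 unadjusted and 3.345/sqrt(2) = 2.365 for Tukey over three pairs.

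| Contrast | Difference (mmHg) | Noncentrality | Tukey | Unadjusted |
|---|---|---|---|---|
| TG-CG | 11.2 | 3.60 | 89.1% | 94.8% |
| UG-CG | 6.2 | 1.99 | 35.8% | 50.9% |
| TG-UG | 5.0 | 1.61 | 22.8% | 35.9% |

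A simulation of 200,000 trials gives 22.8% for TG-UG under Tukey. Bonferroni over the three pairs gives 21.2%.

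**4. Allow for the planned baseline covariate.** The standard error becomes 3.108 × sqrt(1 - r²), with 161 degrees of freedom. For TG-UG:

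| Assumed r | Tukey | Unadjusted |
|---|---|---|
| 0.3 | 25% | 39% |
| 0.5 | 31% | 45% |
| 0.6 | 36% | 52% |
| 0.7 | 46% | 61% |

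**5. Scale.** If all 69 per arm were retained, TG-UG would have 29.0% under Tukey (no baseline gain). For 90% power on TG-UG without baseline gain, 224 evaluable per arm would be needed unadjusted, or 281 with Tukey.

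**The case against.** **The 23% is the least favourable figure.** This stands. It gives no credit for the baseline covariate, and Tukey is offered only as an example. A reader might take 23% as the power of the planned analysis, but the document does not fix enough to say so. A range is the honest statement. Even its favourable end, 61% with no multiplicity adjustment and an assumed correlation of 0.7, is well short of 90%.

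**Omnibus sizing followed by pairwise tests is common, and an analysis plan may name the primary test or contrast.** This also stands, so the absence of a named primary contrast is not held against the protocol. The sentence on comparing marginal means among three groups is compatible with an overall test first. What remains does not depend on a missing document: the protocol gives one power figure, and that figure does not describe the pairwise comparisons it also states.

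**The trial is described as preliminary, and one of its two stated comparisons is well powered.** Both are true. TG versus CG has 89% under Tukey and more with baseline adjustment, and the aims do not rank TG versus UG first. Preliminary status can justify modest power. It does not make 90% the right description of the weaker contrasts.

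**A reader might infer that section 2.7 also shifts the primary time point**, because it speaks of each time point and of the end of follow-up. The document does not support that. The abstract and section 2.5.1 both fix the primary outcome at the end of the 3-month intervention, and section 2.7 describes a general model covering both visits.

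**Conclusion.** The point holds as a mismatch between the stated power and the stated inference. It is not an arithmetical error: 55 per arm and 207 in total are correct for the omnibus test. Nor is the trial underpowered throughout, since TG versus CG is adequately covered.

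The shortfall lies in UG versus CG (36% with Tukey, 51% unadjusted, no baseline gain) and above all in TG versus UG. For the latter, power is 23% with Tukey and 36% unadjusted with no baseline gain, and 25-46% and 39-61% respectively over assumed correlations of 0.3 to 0.7. These figures rest on the protocol's own means and SD, 55 evaluable per arm, and 16.3 read as the month-3 SD. If the Bonferroni step across outcomes also covers the primary outcome, power is lower still.

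**What to change.** 1. **Section 2.2.1:** label the 90% as power for the 2-df omnibus test. Beside it, state month-3 power for each of the three contrasts, as a range over the assumed baseline to month-3 correlation.
2. **Section 2.7:** state that TG versus UG is reported as an estimate with a 95% CI, and that a non-significant result is not evidence of no added TCM benefit.
3. **Optional, section 2.7:** make the 2-df group test at month 3 the primary test at 0.05 and, only if it is significant, test the pairs at 0.05 each. With exactly three arms this is a closed test with strong family-wise control, and it brings the primary test into line with the sample-size calculation.
   - It needs the primary outcome to be exempted from the Bonferroni split with the key secondary outcomes. A split over just two outcomes would cut omnibus power from 90% to 85% (no baseline gain).
   - The pairwise intervals are no longer simultaneous and must be labelled so.
   - It raises TG versus UG only to about 36% before baseline adjustment, so items 1 and 2 are needed either way.

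The cost is wording in two sections and a less favourable stated power for two of the three contrasts. No additional patients are required.

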#### Inclusion and exclusion criteria

2.2.2

##### Inclusion criteria

2.2.2.1

Age ≥ 18 years; confirmed diagnosis of hypertension, type 2 diabetes, and/or hyperlipidemia as multimorbidity; Proficient in using a smartphone and capable of operating applications such as WeChat; Independent in daily living, mentally competent, and able to communicate clearly; able to complete questionnaires and willingness to participate.

##### Exclusion criteria

2.2.2.2

Presence of severe impairment in vital organs such as the heart, liver, or kidneys; Received radiotherapy or chemotherapy within the past 6 months; pregnant or breastfeeding women; current participation in other clinical studies.

### Randomization and blinding

2.3

#### Randomization

2.3.1

A computer-generated randomization sequence will be used. The sequence will be generated in Excel by an independent statistical expert with no conflict of interest before participant enrollment. To ensure allocation concealment, a study coordinator (not involved in recruitment, enrollment, or intervention delivery) will manage the randomization process. After screening, included participants will receive a unique non-sequential identifier (e.g., “ID-001”), linked only to the allocation information and not to intervention details. The study coordinator will assign participants to groups based on this identifier and provide group assignment only to the intervention implementation team, ensuring that other personnel (including recruiters and outcome assessors) remain blinded before the intervention.

